### 3.3 Supplemental consideration regarding the blood analysis methods

Two blood analysis methods will be applied in this project: (1) blood analysis performed by the research group of [name]. [name] (Department of Sports Medicine, University of Tübingen, Germany); (2) TruCulture performed by the Natural and Medical Sciences Institute (NMI) at the University of Tübingen (Germany). In a supplemental consideration it will be evaluated whether reliability (primary objective) and/or the correlation (secondary objective) may be improved by one of the two blood analysis methods. All analytical methods are established standards using CE-certified instruments and there will be no methodological development of invitro-diagnostics.

## 4 Study design and population

A consultation by the Center of Clinical Trials (*Zentrum für klinische Studien*, ZKS) in Tübingen took place on June 4, 2019. The present experimental design, i.e. an observational cross-sectional study, was determined in a biometric consultation by [name]. [name] on March 13, 2019 and a clarification of the required sample size in a biometric consultation by [name]. [name] on February 10, 2020.

### 4.1 Study population

The study population consists of 20 individuals exposed to high physical workload (exposed group) of the upper extremity and 20 individuals exposed (unexposed control group) to low physical workload. The exposed group is in the focus of this research project and should consist of ten women and ten men with highly stressful occupational activities of the hands (e.g., upholsterer as profession), who report minor to severe recurrent pain in the elbow/forearm/hand-area. Participants of the unexposed control group should also consist of 10 women and 10 men but with only low exposure to physical workload and no musculoskeletal pain. Participation is on a voluntarily basis, meaning that the subject is always free to stop participation in the study without justification.

### 4.2 Participant recruitment

Recruitment of the subjects will be through the companies *Mercedes-Benz Group AG* (Stuttgart, Germany – former Daimler AG) and *Robert Bosch Fahrzeugelektrik Eisenach GmbH* (Thüringen, Germany) that have confirmed their support in Letters of Intent they wrote to us (see **Attachment A**). Potential subjects will be recruited exclusively from plants in the extended region of Tübingen (up to 75 min by car). If necessary, further companies with suitable workplaces in the area of Tübingen

will be recruited. For this purpose, we use the contacts of our institute with the occupational health and safety services of various companies.

#### 4.3 Allocation, blinding and randomization

Due to design of the study, which is not an intervention study, allocation and blinding of experimenters and participants is not applicable.

Since this is a cross-sectional study, randomization of intervention or control arm is not applicable. However, measurements are randomized where possible.

The individuals will be studied over a period of eleven to seventeen weeks with data assessment once per two weeks. The choice of the weekday of data assessment (Mon, Wed, Fri) (reflecting the previous dose of exposure) is to be randomized for the twenty subjects in each group over the eleven to seventeen weeks, with the requirement that each weekday is included twice. We apply this requirement to the extent that it is logistically possible for both company and subject as well as physician and researcher.

#### 4.4 Eligibility criteria

##### 4.4.1 Inclusion criteria

The following criteria will be used for recruitment eligibility:

##### Exposed group

- Workplaces where loads on hands and arms exceed the action limit of the HAL TLV (Hand Activity Level Threshold Limit Values; Hoehne-Hückstädt et al., 2007). These limits from the American Conference of Governmental Industrial Hygienists were developed with the goal of preventing work-related illnesses.
- Workload analysis: a daily repetitive strain of at least five hours on one or both hands and at least four days a week with a strain intensity above the action limit of the HAL TLV (Kapellusch et al., 2018).
- Employment: a minimum of one-year employment to above described workplaces at the time of study inclusion.
- Musculoskeletal pain: the study population should suffer from varying degrees of musculoskeletal pain in the elbow/forearm/hand-area, which will be assessed using the Cornell Musculoskeletal Discomfort Questionnaire (Kreuzfeld et al., 2016). Ideally, the population covers the whole range from no pain to very severe pain. However, subjects have to be able to work.

##### Unexposed control group

- Workplaces without physical loads based on the basic screening tool to detect physical stress at work (BAuA, 2022, p. 1) as provided by the Federal Institute for Occupational Safety and Health (*Bundesanstalt für Arbeitsschutz und Arbeitsmedizin*; BAuA), such as office work.
- Employment: a minimum of one-year employment to above described workloads at the time of study inclusion.
- Musculoskeletal pain: the study population should not suffer from musculoskeletal pain within the last four weeks, which will be assessed using the Cornell Musculoskeletal Discomfort Questionnaire (Kreuzfeld et al., 2016).

##### 4.4.2 Exclusion criteria

The following criteria will be used for recruitment eligibility:

- Status after accident and/or systemic diseases that affect joints or muscles and/or are associated with acute and chronic inflammations.

- Exposed group: Musculoskeletal pain that is not localized in the elbow/forearm/hand-area and that is equally or more severe than in the elbow/forearm/hand-area examined in the current study, as assessed by the Cornell Musculoskeletal Discomfort Questionnaire (Kreuzfeld et al., 2016).
- Unexposed control group: Relevant physical demands in the workplace according to the basic screening tool to detect physical stress at work (BAuA, 2022) at study inclusion.
- Relative and absolute contraindications for repeated blood sampling, such as: fear of blood sampling (relative), taking anticoagulants (absolute), few suitable veins that should only be used for therapeutic interventions (absolute).

#### 4.5 Power analysis

The focus of the statistical analysis is the correlation between indicators of chronic inflammation (biomarkers) and the severity of the musculoskeletal complaints in the elbow/forearm/hand-area. We are not aware of any studies on the temporal stability of blood parameters in work-related musculoskeletal pain. Therefore, the necessary knowledge to calculate an optimal amount of measurement repetitions is lacking. The present study is a preliminary study, and the number of nine (at least 6 per subject) measurement repetitions (1 / two weeks) is primarily determined by limiting the number of blood samples required in this preliminary study. Both the median and second lowest values during the measurement period will serve as indicators of the severity of chronic inflammation in the sense of a conservative approach. The correlations between the inflammation parameters and the severity of musculoskeletal pain will be calculated using the Spearman's rank correlation coefficient  $\rho$ . With 20 subjects of the exposed group, the significance limit of Spearman's  $\rho$  for a margin of error of  $\alpha$  of 10% is 0.38, which roughly corresponds to a variance clarification of ~15%. Since further clarification of our hypothesis with the methods tested here would only be meaningful if there was a clear correlation, the study achieves the required significance with a sample size of 20 subjects. The number of subjects in the unexposed control group will be equal as in the exposed group.

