### 3 Study objectives

The results of the animal experiments (cf. 2.3) published so far are to be verified in humans. To this end, a preparatory methodological study is to be carried out in order to clarify open methodological aspects for the subsequent implementation of a long-term study (cohort of occupationally exposed persons). Against the background depicted in 2.3, 2.4, and 2.5, we will focus on CRP, IL-6 and IL-1 $\beta$  as potential markers of inflammation. In the proposed preliminary study, we have two study objectives:

1. Assess the reliability of inflammation parameters by repeated measurements.
2. Conduct a cross-sectional exploratory investigation to determine whether clearly significant correlations between signs of chronic inflammation (in the blood serum) and musculoskeletal (upper-extremity) pain can be demonstrated in occupationally stressed subjects.
3. Compare signs of chronic inflammation (in the blood serum) between individuals exposed to high physical workload in the upper extremities and individuals with low physical workload.

A subsequent long-term study (not part of this ethics proposal) will then show whether the corresponding correlations can be understood as causal mechanisms. In this follow-up project, newcomers to stressful occupations will be followed for one to two years. A causal chain would consist of a chronic inflammatory condition following acute epicondylitis if recurring stresses occur during the healing phase. Subsequently, chronic recurrent subclinical complaints would persist. To elaborate the design of a subsequent long-term study, results on the following aspects are expected:

- Reliability/repeatability of the measured values, especially the parameters obtained from the blood serum, in order to determine the parameters suitable for the long-term study and to determine the length of the time intervals between measurement repetitions.
- Relationship between signs of chronic inflammation and pain frequency/intensity and intra- and interindividual variability of measurement parameters for sample size calculation for the follow-up study.

- Exposure assessment by observational methods: evaluation of the literature (e.g., Klußmann et al., 2010; Takala et al., 2010) and selection and testing of two methods in the field to identify the most appropriate method for the follow-up study (practicability).

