### 5.2.3 Work package 3: Carrying out the measurements including data preparation

*This work package is estimated to last about 240 working days (~11 months).*

Study participation for all subjects takes about twelve to eighteen weeks, including a pre-assessment or baseline assessment at study inclusion (one visit,  $T_0$ ), and an eleven-to-seventeen-week observation period (nine visits,  $T_1$ - $T_9$ ). It is desired to start measuring the first recruited subject in “Month 8” (i.e., November 2023) of the study’s timeline and to finish measuring the last recruited subject in “Month 18” (i.e., September 2024) of the study’s timeline (cf. **Figure 2**). We assume that 25 persons have to be recruited in each group to finally have data of 20 subjects with at least 6 repeated measurements. Six repeated measurements will enable us to monitor the selected inflammation parameters for about 4 months.

The collection points at which measurements are taken are tabulated in **Table 1** and visualized in **Figure 3**.

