#### 6.6 Inflammation parameters in blood

Trained staff (i.e., *Medizinische Fachangestellte*) will collect venous blood at  $T_0$  and weekly during the observation period ( $T_1$ - $T_9$ ). Approximately  $\sim 11$  ml of blood is taken during the screening ( $T_0$ ) and  $\sim 16$  ml of blood is taken during each of the six to nine collection points during the observation period ( $T_1$ - $T_9$ ). Using the venous blood samples, laboratory parameters will be assessed, i.e. indicators of inflammation (IL-6, CRP, and IL-1 $\beta$ ) that have been shown to be significantly elevated in the blood serum in persistent tendinitis in animal studies (Gao et al., 2013). The six to nine blood samples ( $T_1$ - $T_9$ ) will be collected from each subject, each at the same time of day, weekly. A blood analysis for determining IL-6 and IL-1 $\beta$  by enzyme-linked immunosorbent assay (ELISA) will be executed by the

research group of [name]. [name], working at the Department of Sport Medicine (University of Tübingen, Germany) as well as standard analysis of CRP and IL-6 by the UKT Central Laboratory.

The inter-individual variability (heterogeneity) in immune response is high (Duffy et al., 2014). Therefore, an approach, developed by HOT Screen GmbH and used by the NMI at the University of Tübingen for the determination of inflammation indicators described above, will be used additionally. It is presumed that this approach will reduce inter-individual variability and increase repeatability of the blood markers. The NMI has been cooperating with HOT Screen (GmbH, Reutlingen, Germany) for many years on the topic of whole blood stimulation tests. [name] has developed a method for this purpose called TruCulture, which makes it possible to analyse small drug-induced changes in the activity of immune cells under highly standardized conditions in the context of clinical studies. Similarly, physical activities can be visualized with this system (blood sampling before exercise and after exercise). TruCulture has proven its potential in the reliable determination of immune cell activities in numerous studies (e.g., Duffy et al., 2017; Duffy et al., 2014; Goepfert et al., 2021; Urrutia et al., 2016). TruCulture is an established standardized functional immunophenotyping method. There will be no development of in-vitro-diagnostic within the present study.

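### The second lowest value is not comparable between people who gave six and people who gave nine samples; put it on a common six-sample basis (minor)

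*Protocol*

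**What the plan says.** Protocol section 4.5 (repeated in the Synopsis under study design and sample size) defines the per-person summary: "Both the median and second lowest values during the measurement period will serve as indicators of the severity of chronic inflammation". It describes this choice as conservative and does not rank the two indicators. The next step it names is Spearman's correlation between the inflammation parameters and pain severity in the exposed group.

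The number of samples behind each summary is allowed to vary:

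- Section 4.5: "the number of nine (at least 6 per subject) measurement repetitions (1 / two weeks".
- Section 5.2.3: 25 people are recruited per group "to finally have data of 20 subjects with at least 6 repeated measurements".
- Section 6.6: blood is drawn at "each of the six to nine collection points during the observation period".
- Section 4.3: "The individuals will be studied over a period of eleven to seventeen weeks with data assessment once per two weeks".

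The protocol does not equalise or adjust for the number of samples. Section 3 also plans to "Compare signs of chronic inflammation (in the blood serum) between individuals exposed to high physical workload" and those with low workload, without saying which per-person summary that comparison uses.

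**The concern.** The median estimates the same point of a person's distribution whether it comes from six samples or nine. The second lowest value does not. For a given person, a seventh, eighth or ninth sample can only lower it or leave it unchanged. One label therefore covers different quantities, and Spearman's rho ranks them together.

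If people with more pain, or one of the two groups, tend to give fewer samples, the indicator will be higher in them without any difference in inflammation. Samples are taken before a shift (section 5.4) and exposed participants must be able to work (section 4.4.1), so absence from work could cost a visit. If that absence went with pain or exposure, the error would point in the direction of the study hypothesis. Section 4.5 calls the pain correlation the focus of the analysis and makes further work depend on finding a clear one.

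**Working it through.** **Inputs from the protocol.** Six to nine samples per person (sections 4.5, 5.2.3, 6.6); 20 people per group (section 4.5: "The number of subjects in the unexposed control group will be equal as in the exposed group"); the significance limit for rho, "of 10% is 0.38, which roughly corresponds to a variance clarification of ~15" percent (section 4.5).

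**Assumptions.** The protocol gives no within-person variability. I take normal values (for example log concentrations) and an intraclass correlation (ICC, the between-person share of variance) of 0.3, 0.5 and 0.7.

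**The plan's own figure.** With n = 20 and two-sided alpha 10%, r = t/√(n − 2 + t²) with t at 18 df gives 0.378. The permutation probability of |rho| ≥ 0.38 is 0.099, and 0.38² = 14.4%. The stated limit reproduces and is not affected by this point.

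**Expected position of the second lowest value.** For k exchangeable continuous values, the expected quantile level is 2/(k + 1). The expected value under normality comes from numerical integration.

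| Samples k | Expected quantile level | Expected value (within-person SD from own mean) |
|---|---|---|
| 6 | 2/7 = 28.6% | −0.642 |
| 7 | 2/8 = 25.0% | −0.757 |
| 8 | 2/9 = 22.2% | −0.852 |
| 9 | 2/10 = 20.0% | −0.932 |

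Six versus nine: −0.642 − (−0.932) = 0.29 within-person SD. On a log-normal scale this is a ratio of 1.09, 1.15, 1.23 or 1.27 for an assumed within-person coefficient of variation of 0.3, 0.5, 0.8 or 1.0.

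**Group comparison, no true difference** (20 vs 20, simulated, Mann-Whitney at nominal 5%, second lowest value):

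| Visits | ICC 0.3 | ICC 0.5 | ICC 0.7 |
|---|---|---|---|
| all 6 vs all 9 | 18.4% | 12.0% | 8.1% |
| all 7 vs all 9 | 9.6% | 7.4% | 6.4% |
| all 8 vs all 9 | 6.0% | 5.4% | 4.9% |
| counts mixed, means 7 vs 8 | 6.3% | 6.2% | 5.5% |

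A repeat of the first row gave 18.7%, 13.1% and 8.7%.

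**Correlation, biomarker unrelated to pain** (n = 20, |rho| ≥ 0.38, nominal 10%):

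| Visits | ICC 0.3 | ICC 0.5 | ICC 0.7 |
|---|---|---|---|
| ten with most pain give 6, the rest 9: mean rho | +0.15 | +0.11 | +0.08 |
| same: false positives | 16.5% | 13.9% | 12.0% |
| ten with most pain average 7, the rest 8: mean rho | +0.05 | +0.04 | +0.03 |
| same: false positives | 10.5% | 9.4% | 10.4% |
| counts random with respect to pain: false positives | 9.9% | 9.7% | 9.7% |

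**Controls.** With equal counts (6 vs 6 or 9 vs 9) the second lowest value gives 4.7% to 5.0% at nominal 5%. The median under 6 vs 9 gives 4.7% to 5.1%.

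**The case against.** The strongest case on the other side is that the harm needs visit counts to go with pain or group, and no section says that they do.

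- **Planned duration.** The 11-to-17-week range applies to both groups. At two-week spacing, six visits span 5 × 2 = 10 weeks (so 11 calendar weeks) and nine span 8 × 2 = 16 (so 17). Part of the variation may simply be planned duration.
- **Other influences on attendance.** Section 4.3 puts scheduling limits down to logistics on all sides, and section 7.2 pays EUR 200 after the eighth and ninth measurements, an incentive to complete.
- **The safeguard.** The median is specified alongside and does not shift, so disagreement between the two would be visible.
- **The stakes.** The primary objective is reliability (section 3.1). The pain correlation is secondary (section 3.2) and described as exploratory (section 3).
- **The analysis plan.** Handling of unequal counts is the kind of detail that a SAP often settles.

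Most of this stands, and it limits the size of the point. It does not remove it. The protocol itself fixes both the indicator and the varying count, and the direction of the shift needs no assumption about attendance. A sound median also does not make the other named indicator comparable, and section 4.5 gives no rule for the case where the two disagree.

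A reader might infer more: that the plan builds in a false-positive result for the study hypothesis, in both the correlation and the group comparison. The documents do not support that. The link between attendance and pain or group is only an inference from sampling before a shift. The larger error rates need whole groups, or whole pain halves, at six versus nine visits. Section 4.5 ties the indicator explicitly only to the pain correlation; the Abstract and sections 3.2 and 5.2.4 describe the group comparison in terms of biomarker concentration.

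**Conclusion.** The point holds as a minor one. Second lowest values from people with six and with nine samples are not comparable. The shift is exact in quantile terms (28.6% against 20.0%) and at most 0.29 within-person SD under normality. Those with fewer visits look more inflamed, which sits badly with calling the indicator conservative.

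With counts unrelated to pain and group, the consequence is noise and the error rates hold. With a one-visit average gap, the correlation stays near its nominal 10% and the group test rises to about 6% at nominal 5%. Only in the extreme of six versus nine visits for whole groups does the group test reach about 8% to 19%, for assumed ICCs of 0.7 to 0.3. These rates rest on normal values and on ICCs that the protocol does not give. The median, the 0.38 limit and the primary reliability objective are not touched.

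**What to change.** State in section 4.5, before results are seen, that the second lowest value is computed on a common basis of six samples for everyone. There are two ways:

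- **Average over all six-sample subsets of a person's valid samples.** This uses all the data and is a fixed weighted mean of the ordered values. With nine samples there are 84 subsets, and the second to fifth lowest values get weights 35, 30, 15 and 4 out of 84. The expected quantile level is (35 × 0.2 + 30 × 0.3 + 15 × 0.4 + 4 × 0.5)/84 = 24/84 = 2/7, the same as with six samples.
- **Use six samples per person, balanced by weekday where possible.** Simply taking the first six could upset the section 4.3 requirement that each weekday occurs twice.

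Also name the median as the main indicator, since section 4.5 ranks neither, and report the number of samples by group and by pain level. A mixed-model person mean on log concentration would use all samples, but it describes the average level, not the low level the plan chose, so it is not a like-for-like replacement.

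The cost is a few sentences and slightly more analysis work, or a small loss of information if only six samples are used. No extra visits, blood or participants are needed.

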### 5.3 Study outcomes

The study will include a large number of measurement parameters in order to determine a few optimally selected measurement parameters for the planned elaborate long-term cohort study. An overview is presented in **Table 1**.

**TABLE 1.** OVERVIEW OF THE INCLUDED MEASUREMENT PARAMETERS AND COLLECTION POINTS.

| Method                                           | Parameter                                                                                                                                                                                                                            | Time point                                                                                                                     |
|--------------------------------------------------|--------------------------------------------------------------------------------------------------------------------------------------------------------------------------------------------------------------------------------------|--------------------------------------------------------------------------------------------------------------------------------|
| Exposure at work                                 | Determining the hand activity                                                                                                                                                                                                        | Inclusion (T 0 )                                                                                                    |
|                                                  | Level and variability of workload determined using two standardized methods: the observation methods are determined based on literature (Klußmann et al., 2010; Takala et al., 2010) and video analyses of the respective workplaces | 11-to-17-week observation period (T 1 , T 4 , T 7 , T 9 )                          |
| General medical examination for inclusion        | Anamnesis                                                                                                                                                                                                                            | Inclusion (T 0 )                                                                                                    |

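### Section 4.5 justifies n=20 and the value of a follow-up by a one-test limit (rho 0.38) without naming the marker, indicator or pain rating it applies to

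*Protocol*

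**What the plan says.** Protocol section 4.5 makes the correlation between inflammation indicators and complaint severity the focus of the statistical analysis. Its sample-size argument is a critical value: "With 20 subjects of the exposed group, the significance limit of Spearman's" rho at an error margin "of 10% is 0.38, which roughly corresponds to a variance clarification of ~15" per cent. It then ties the worth of continuing to the result, "Since further clarification of our hypothesis with the methods tested here would only be meaningful if there was a clear correlation", and concludes that 20 subjects achieve the required significance.

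The quantities that could enter this correlation are spread over several sections:

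- Section 3 on markers: "we will focus on CRP, IL-6 and IL-1" beta.
- Section 4.5 on indicators: "Both the median and second lowest values during the measurement period will serve as indicators of the severity of chronic inflammation".
- Section 6.3 lists four pain ratings: current pain, night pain, and weekly maximum and minimum.
- Section 3.3 has two blood analysis methods. It is to be "evaluated whether reliability (primary objective) and/or the correlation (secondary objective) may be improved by one of the two blood analysis methods".
- Section 5.3 describes "a large number of measurement parameters in order to determine a few optimally selected measurement parameters" for the later cohort.
- Section 3 expects the relationship between inflammation signs and pain to serve follow-up planning, together with "intra- and interindividual variability of measurement parameters for sample size calculation for the follow-up study".

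No section names the marker, indicator or pain rating that has to reach 0.38.

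**The concern.** A critical value has its stated error rate only for the test it was derived for. Section 4.5 derives one for a single correlation and uses it as the sole numerical justification of n=20. The Protocol then describes a set of correlations from which a passing one could be picked after the data are seen. Unless the pair is fixed beforehand, the 10% in section 4.5 does not describe the chance of a positive finding when inflammation and pain are unrelated.

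The second issue is estimation. If the reported pair, or the preferred blood method, is selected because its correlation is larger in these 20 people, that correlation overestimates the true one on average. The same study is meant to supply planning figures for the cohort.

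**Working it through.** **Reproducing the limit.** With n = 20 there are 18 degrees of freedom and rho_crit = t / sqrt(18 + t²).

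- Two-sided 10%: t = 1.734, so rho_crit = 1.734 / sqrt(18 + 3.007) = 0.378.
- One-sided 10%: t = 1.330, so rho_crit = 0.299.
- Random permutation: P(|rho| ≥ 0.38) = 0.098 and P(rho ≥ +0.38) = 0.049.
- Variance share: 0.38² = 0.144, or about 15%.

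Section 4.5 does not state sidedness, but its 0.38 is a two-sided 10% limit (5% per tail) for one test.

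**Counting candidate pairs.** 3 markers × 2 indicators × 4 pain ratings = 24. If every marker were read by both blood methods, the count would be 48. Clinical findings (section 3.2) and pressure pain thresholds (section 6.4) are not counted. With a single pain item the count is 3 × 2 = 6.

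**Chance of at least one passing pair under no association.** Independent tests would give 1 − 0.90^24 = 0.92, but these tests overlap, so that figure is too high. The Protocol gives no correlations among the measures. The following were assumed and varied: markers 0 to 0.7, median with second lowest 0.8 to 0.95, pain items 0.3 to 0.9, and the two blood methods 0.3 to 0.9. The central scenarios use markers at 0.3 to 0.5, pain items at 0.7 to 0.8, and indicators built from six simulated visits with half the variance between persons. Simulated results for n = 20 are:

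| Tests | Any \|rho\| ≥ 0.38 | Any rho ≥ +0.38 |
|---|---|---|
| 1, fixed in advance | 9.8% | 4.9% |
| 6 (one pain item), central | about 32–35% | about 17–18% |
| 24, central | about 60–69% | about 31–39% |
| 24, full assumed range | about 46–85% | about 23–56% |
| 48 (both blood methods), assumed range | about 61–96% | about 32–71% |

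The simulated values carry up to about a percentage point of Monte Carlo error. On average 24 × 0.098 = 2.4 of 24 pairs pass by chance.

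**Effect of the second indicator.** In the central scenarios with four pain ratings, using the median alone gives 48–56% two-sided, and adding the second lowest value gives 59–67%. It adds chances to pass but does not double the probability, because the two indicators are strongly related.

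**What an adjusted limit would be.** Bonferroni over 24 two-sided tests uses 0.10/24 = 0.0042, with t = 3.28 and rho_crit = 3.28 / sqrt(18 + 10.76) = 0.61. The simulated 90th percentile of the largest |rho| is 0.55 to 0.61. An analysis that adjusted for all 24 pairs would therefore no longer use 0.38, and the argument in section 4.5 would lapse.

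**The case against.** Several counter-arguments have force.

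- **No explicit rule.** Section 4.5 does not say that one passing pair suffices, and it does not equate the 0.38 limit with the correlation it calls for. Sections 5.1 and 5.2.5 plan the grant application without any correlation threshold. This stands, so the probabilities above are conditional on that reading.
- **Direction.** The model in section 2.5 expects more inflammation with more pain, so a negative correlation would not support it. This also stands. For positive correlations only, the central 24-test figure is 31–39% and the average largest positive rho under no association is 0.29 to 0.33, below 0.38. A reader might infer that a study with no true association would pass more often than not, or that the criterion could hardly stop a false hypothesis. The Protocol does not support either as a general statement.
- **Basis of selection.** Section 3 ties the choice of parameters mainly to reliability, the primary objective, and section 5.3 does not mention choosing by correlation. Only section 3.3 allows the correlation to count, and only between blood methods.
- **Follow-up size.** A reader might infer that the cohort will be undersized by some stated factor. Nothing says it will be sized on the largest observed rho. The follow-up is a cohort of newcomers observed for one to two years, so a sample-size formula for one cross-sectional correlation does not describe it.
- **Exploratory status and the SAP.** Section 3 calls the investigation exploratory, and pair choice or multiplicity may be set in an SAP that is not shown. This does not remove the point. The same sentence in section 3 looks for clearly significant correlations, and section 4.5 itself fixes the one-test limit as the sample-size argument. An SAP that names one pair would agree with section 4.5, whereas one that adjusts over many pairs would contradict it.

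**Conclusion.** The point holds in a limited form. The 0.38 limit is correct for one pre-named correlation, and section 4.5 relies on it without naming one. On the open reading, the chance of a passing pair under no association is about 46–85% two-sided or 23–56% positive only for 24 tests. With one pain item it is about 32–35% or 17–18%. Every figure lies above the stated 10% (5% per tail), but its size rests on assumed correlations among measures, on how many pairs are tested, and on one pair being enough. Upward bias in the planning estimate follows only if the pair or blood method is chosen by its observed correlation, which section 3.3 permits for the method. How far this would affect the cohort's size cannot be derived from the Protocol.

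**What to change.** Before analysis, amend section 4.5 (and the matching synopsis text) to name one marker with its assay, one of the two indicators and one pain summary as the single correlation to which 0.38 applies. State the expected direction and whether the test is one- or two-sided: at 0.38 a directional test has an error rate of about 5%, and a two-sided test about 10%. Report all other pairs, including the comparison of blood methods, as exploratory estimates with confidence intervals and no significance claims. State in section 3 that follow-up planning will use the named pair with its uncertainty, not the largest observed rho.

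The cost is wording only: no further subjects, visits or samples. The downside is that the other pairs lose their significance claims.
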